### Second randomisation: emergence phase of anaesthesia

Participants will be randomised to conversion to a propofol infusion for emergence from anaesthesia (Intervention 2) versus control (standard emergence from volatile anaesthesia).

This intervention will be achieved by infusion of propofol 400 mg/h and simultaneous reduction of inspired desflurane concentration during the final 10–20 min of surgery. Boluses of propofol may be given as required to keep acceptable quantitative EEG index values until surgery is complete. Total doses of propofol administered are likely to be in the range 1–3 mg/kg, which is comparable to the effective dose in children.

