#### Primary outcomes

##### Intervention 1

Oscillatory EEG alpha power during the maintenance phase of anaesthesia

##### Intervention 2

Oscillatory EEG alpha power during the emergence phase of anaesthesia

Our primary trial outcomes are EEG outcomes (rather than clinical outcomes) because it is important firstly to determine whether the interventions, which are novel, do indeed have the anticipated effects on the intraoperative EEG parameters. Oscillatory alpha [12] is chosen as the outcome of neurophysiological interest because the total power in the frequency band is subject to general slowing of the EEG signal, and so the frequency of the alpha oscillation can drift outside the traditionally defined alpha frequency band.

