### Statistical analysis and power calculations

We intend to recruit 600 participants. The 2 × 2 factorial design will result in 300 patients assigned to the maintenance phase intervention and 300 to the emergence phase intervention (see Fig. 1). This will ensure that the study will be well-powered for the primary EEG outcomes and sufficiently powered to detect moderate-large effects in the secondary clinical outcomes. Our primary analyses will be intention to treat; however, per-protocol analyses will also be reported. For the primary outcome for the maintenance phase *Alpha Max* intervention, alpha power in groups A and B (Fig. 1) pooled together will be compared to groups C and D. For the primary outcome for the emergence phase intervention, groups A and C (Fig. 1) will be compared to groups B and D pooled. The crude difference will be reported as the primary outcome; however, an adjusted estimate will also be provided for the emergence outcome. This will include an interaction term for the maintenance phase intervention, since one might reasonably expect alpha power in the emergence phase to correlate with alpha power in the maintenance phase.

EEG analysis will be performed using customised script in MATLAB. Our previous summary data suggest that a mean oscillatory alpha power of 4.75 dB with standard deviation of 2.1 dB might be expected in a general surgical population. Therefore, an estimated 230 patients are required to have 95% power to detect an increase in oscillatory alpha of at least 1 dB (equivalent to ~ 20% relative increase in alpha power in response to the fentanyl) in the intervention group compared with the control group (two-tailed alpha 0.05, beta 0.05); thus, with a planned total of 300 patients per group we are comfortably overpowered for this outcome.

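### The supplementary adjusted emergence estimate rests on an interaction with the maintenance allocation, which does not address the correlation given as its reason; measured maintenance alpha plus a main effect of allocation would.

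*Protocol article*

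**What the plan says.** Under Primary outcomes, the outcome for Intervention 2 is "Oscillatory EEG alpha power during the emergence phase of anaesthesia". The outcome for Intervention 1 is the same quantity in the maintenance phase, so maintenance alpha is already to be derived for the trial.

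Under Statistical analysis and power calculations, the emergence comparison pools groups A and C against B and D. On reporting, the article says: "The crude difference will be reported as the primary outcome; however, an adjusted estimate will also be provided for the emergence outcome". Of the adjusted estimate it says: "This will include an interaction term for the maintenance phase intervention". The reason follows in the same sentence: "one might reasonably expect alpha power in the emergence phase to correlate with alpha power in the maintenance phase". No other term is named for this model.

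Intervention 2 starts late. It is a propofol infusion with "simultaneous reduction of inspired desflurane concentration during the final 10–20 min of surgery". Under Randomisation and blinding, the researcher collecting the intraoperative EEG performs the randomisation shortly before anaesthesia begins, and the case anaesthetist is not blinded.

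**The concern.** The reason given is a correlation between two measurements: alpha in maintenance and alpha in emergence. The term given is a product of two allocations. A correlation between an earlier and a later measurement is handled by putting the earlier one in the model as a covariate. An interaction answers another question, namely whether switching to propofol has a different effect in patients whose maintenance was titrated to alpha.

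Two things follow. First, the adjusted estimate does not do what its stated reason calls for. Secondly, its meaning depends on coding that the article does not state: once an interaction is in the model, the emergence coefficient is an average effect or an effect in one maintenance arm, according to how the factors are coded. A reader could take the difference between the crude and adjusted results for the effect of adjustment when it is a change of estimand.

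**Working it through.** **Inputs from the plan** (Statistical analysis and power calculations): "mean oscillatory alpha power of 4.75 dB with standard deviation of 2.1 dB"; target "an increase in oscillatory alpha of at least 1 dB"; "two-tailed alpha 0.05, beta 0.05"; 230 patients required; 300 per pooled arm planned; 1:1 allocation to each factor.

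**Assumptions.** The 2.1 dB SD applies to both phases (the article does not say which phase it describes). The correlation r between maintenance and emergence alpha is not given, so it is shown at 0.3, 0.5 and 0.7.

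**1. The plan's own figure.** n per arm = 2 × (1.960 + 1.645)² × 2.1² / 1² = 114.6, rounded up to 115, or 230 in total. The stated figure reproduces. At 300 per arm the power for 1 dB is 99.99%.

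**2. Crude standard error (SE).** 2.1 × √(2/300) = 0.171 dB. The difference detectable with 95% power is 3.605 × 0.171 = 0.62 dB.

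**3. The interaction under 0/1 coding.** The emergence coefficient is then the effect in maintenance controls only, group C against group D, 150 against 150: SE = 2.1 × √(2/150) = 0.242 dB, which is √2 times the crude value.

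**4. What allocation can contribute.** A 1:1 allocation with a 1 dB effect adds 0.5² = 0.25 to the variance of maintenance alpha. Its share is 0.25 / (2.1² + 0.25) = 0.25 / 4.66 = 5.4%. The share depends on the effect: 1.4% at 0.5 dB, 11.3% at 1.5 dB, 18.5% at 2 dB.

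**5. SE of the emergence effect with each adjustment.** With measured maintenance alpha it is 0.171 × √(1 − r²). With allocation only it is 0.171 × √(1 − 0.054 r²).

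| Assumed r | SE, allocation only | Reduction | SE, measured alpha | Reduction | Equivalent N, 600/(1 − r²) | Detectable difference |
|---|---|---|---|---|---|---|
| 0.3 | 0.171 | 0.2% | 0.164 | 5% | 659 | 0.59 dB |
| 0.5 | 0.170 | 0.7% | 0.148 | 13% | 800 | 0.54 dB |
| 0.7 | 0.169 | 1.3% | 0.122 | 29% | 1176 | 0.44 dB |

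**6. Simulation check** (1,500 trials of 600 patients, 150 per cell, r = 0.5, least squares). The empirical SE was 0.168 crude, 0.168 with allocation and a centred interaction, 0.242 with a 0/1-coded interaction, and 0.147 with allocation and measured maintenance alpha. All four models recovered the 1 dB effect; the simulated data contained no interaction, so the 0/1-coded coefficient had the same target there.

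**The case against.** The strongest reply is that the authors never meant to exploit a patient-level correlation. The second item under Hypotheses says that maximising alpha in maintenance promotes alpha in emergence. That is carry-over from one factor to the other, and the randomised allocation is the right variable for it. This is a fair reading, and on it the 5.4% share is beside the point. But carry-over calls for a main effect of allocation, not an interaction, so term and reason still do not match. The same section separately promises to examine interactions between the interventions, so nothing is lost by taking the interaction out of this estimate.

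A second reply is that the article is condensed and that it plans non-linear mixed-effect modelling where appropriate, for features such as a patient's maximum alpha power. Covariates may well be left to an analysis plan. But that modelling is not tied to this estimate, and here the article does fix a term and a reason.

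A third reply is that measured maintenance alpha has a cost as a covariate. Both allocations are drawn before anaesthesia, and the unblinded anaesthetist controls the agents that move alpha. This stands. A comparison of means by emergence arm can reveal an influence of the allocation but cannot exclude one.

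A reader might infer that a primary result is compromised, or that maintenance alpha is shown to be the main predictor of emergence alpha. The documents support neither. The crude difference is primary and unbiased under randomisation, and its confidence interval already allows for chance imbalance. No correlation is reported.

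**Conclusion.** The point holds for the supplementary adjusted estimate and no further. The interaction term does not address the correlation offered as its reason, whichever way that reason is read. Centred, it adds almost no precision; coded 0/1, it turns the coefficient into the effect in maintenance controls, with an SE of 0.242 dB in place of 0.171 dB.

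Using measured maintenance alpha would improve precision only: about 5%, 13% and 29% off the SE at assumed r of 0.3, 0.5 and 0.7, against about 1% or less for allocation at the planned 1 dB effect. A low r cannot be ruled out from the document, and the gain would then be slight. The crude detectable difference of 0.62 dB is already below the 1 dB target, so the primary test does not need the gain. Its use is a narrower interval for an effect that has not been measured before in this population.

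**What to change.** Keep the crude A + C against B + D difference as the primary emergence result. Define the adjusted estimate as an analysis of covariance with:

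- emergence allocation;
- maintenance allocation as a main effect;
- the patient's mean oscillatory alpha during maintenance as a continuous covariate, from a window that closes before the final 20 min of surgery in all four groups.

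Report the interaction between the two interventions separately, with its coding stated. Show mean maintenance alpha by emergence arm, and describe the adjusted result as supportive. Do not use this covariate when estimating the effect of Intervention 1, which acts on it directly.

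The cost is a change of analysis wording and one more derived EEG variable; the frontal EEG is already recorded. It assumes that the time of the end of surgery is available, so that the same window can be cut in patients who have no propofol switch. Start times of the infusion should be checked against the window, since an early start would let the intervention into the covariate.

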### Ethical considerations

Older patients undergoing surgery constitute a potentially vulnerable population. Participants will be approached and consented by experienced research staff. We plan to only include participants who have given informed consent for surgery (or are expected to give their own consent for surgery) and, thus, would also be expected to be competent to consent to research. In addition, the research team will have discretionary ability to exclude participants should they feel that the patient is unable to sufficiently understand and consent to the study. However, it may be that some patients achieve scores much lower than is expected or normal for their age. It is important that this group is included in the study as they constitute a patient group that will potentially benefit most from the interventions.

Participants will be encouraged to discuss the study with any support people they wish and research staff will explain the study to support persons to aid decision-making. In order to assure that our study participants are capable of understanding the information provided in the informed consent, a further single question screen will be used to detect inadequate health literacy. ‘*Are you confident filling out medical forms by yourself*?’ has been used previously to detect poor health literacy [30]. If the answer to this question is ‘no’ or the pre-operative MOCA score is very low (less than 15/30) and it appears that the patient is unable to fully understand the implications of taking part in the study, they will be excluded from the study and the clinical team will be informed. We will check during the consent process the participant’s wishes about information disclosure should we detect early cognitive impairment and these wishes will be followed. The usual clinical standard of preservation of confidentiality will be preserved; data will not be published or shared in any such way that would reasonably be expected to identify individuals.

## Discussion

As far as we are aware, this will be the first RCT whereby anaesthesia is titrated to the observed frontal EEG alpha oscillation, rather than quantitative EEG index values. Furthermore, we hope to establish the degree of association between intraoperative alpha activity and PACU delirium, which is unclear at present.

Features of anaesthesia and delirium overlap considerably and it is difficult to define when anaesthesia emergence ends. Current nomenclature can be quite confusing with terms such as emergence agitation, hypoactive, hyperactive, PACU delirium and postoperative delirium employed for somewhat similar states, which also fluctuate with time. The syndrome we are evaluating may in fact better be considered a delayed or incomplete neurocognitive recovery from anaesthesia. This clinical relevance of this syndrome is unclear and it is relatively sparsely represented in the literature; however, the small body of existing evidence suggests that PACU delirium is associated with multiple adverse clinical outcomes [31]. With this study we hope to establish whether this is simply a result of existing patient and surgical factors or if optimisation of anaesthesia might be protective.

The optimal assessment tool to measure delirium in the PACU environment is unclear. We have elected to use the 3D-CAM score as our main clinical outcome measure but we will also take the opportunity to evaluate and compare some other candidate scores. A secondary objective of the study will be to evaluate which features of delirium are most closely associated with later adverse outcomes. A recent consensus guideline [20] has recommended routine screening of patients for delirium prior to discharge from the recovery room; however, it does not specify a particular tool. Ideally the assessment tool should identify patients at risk of subsequent deterioration and adverse clinical outcomes. We plan to evaluate the performance of 3D-CAM in this regard, and to possibly create a tool specifically for an immediate post-anaesthesia care episode.

This study has been approved by the New Zealand Health and Disability Ethics Committee ref. 17/NTA/56 and has local intstitution approval at Waikato Hospital. Ethics/IRB approval and local institutional approval will be obtained prior to commencement of the study at other sites. Recruitment began in February 2018 at our primary site with plans for at least two international collaborating sites to join. As of October 2018, we have recruited 60 patients. Data collection is expected take 3–4 years. Dissemination plans include presentations at scientific conferences and publication in peer-reviewed journals.

